Our research team began studying MZRW for functional constipation (FC) in 2006. We found that available studies had significant methodological flaws and lacked replicable validation; thus, clinical findings could not be definitively determined [12]. Therefore, the efficacy and safety of MZRW had to be justified by first determining the optimal dose. The currently recommended dose (5.0 g b.i.d.) was compared with higher (7.5 g b.i.d.) and lower doses (2.5 g b.i.d.); the study was supported by the WooFo Medical Foundation. The dose of 7.5 g b.i.d. was found to have better therapeutic effect than that of 2.5 and 5.0 g b.i.d. among 96 subjects (32 per arm). Second, MZRW in optimal dosage (7.5 g b.i.d.) was compared with a placebo for FC patients with excessive TCM Syndrome in a randomized, double-blind clinical trial, which was supported by the Health and Health Services Research Fund. In this study, 120 subjects were randomized into two arms (60 per arm). Response rates for the MZRW and placebo groups were 43.3% and 8.3% during treatment, and 30.0% and 15.0% in the follow-up period, respectively (*P* <0.05). Those in the MZRW group showed benefits in terms of increased bowel movement, relief in the severity of constipation and straining, and effective reduction in the use of rescue therapy when compared with placebo. These encouraging results suggested that the higher dose, which had not been the recommended dosage in the Clinical Handbook of Chinese Herbal Formulae [13], was in fact safe and effective for alleviating FC when compared with the placebo [14].

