### Sample size calculation

From the results of the placebo-control study, the response rate of MZRW was 43.3% [14]. Assuming the response rates for TCM, senna and placebo were 40%, 20% and 10%, respectively. Therefore, 82 patients per treatment group were deemed sufficient to achieve 80% power in detecting treatment differences, based on two-sided Chi-square test without continuity correction at a significance level of 0.025 (used to maintain the overall significance level at 5%). Further, assuming a 15% dropout rate, we concluded that a total of 291 patients (97 per arm) would need to be recruited to ensure statistically significant results. The calculation is performed using StudySize 2.0 software, London, UK.

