### Statistical analysis

All efficacy and safety analyses will be conducted according to the intention-to-treat (ITT) principle. Missing values will be imputed by the last-observation-carried-forward method. The statistical analysis will be performed using the Statistical Packages of Social Sciences (SPSS) for Windows version 16.0. The statistical significance is defined as two-sided *P* value of <0.05. Baseline characteristics will be reported as mean (SD). Baseline differences among the groups will be assessed with the use of Student’s t-test for normally distributed continuous variables and the non-parametric Mann-Whitney U test for non-normally distributed variables. For categorical variables, chi-squared test or Fisher’s exact test will be used. Comparisons between groups will be conducted by using an analysis of covariance (ANCOVA) with baseline as covariate. All items and subscales will be compared between groups for each 6-week treatment using ANCOVA, with treatment group as a factor in the model and baseline as the covariate. The changes from baseline to endpoint of treatment in scores will be tested with repeated measure analysis of variance (ANOVA). Within group differences will be assessed with paired t-test for normally distributed data and Wilcoxon signed-rank test for non-normally distributed data.

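### The stated 80% power for 82 per arm does not hold at the stated two-sided 0.025, and it is not the power of the planned comparison, which analyses all 97 per arm

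*Protocol article*

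**What the plan says.** All the planning figures are in the protocol article, section Sample size calculation. The rates are introduced as follows: "Assuming the response rates for TCM, senna and placebo were 40%, 20% and 10%, respectively". On these, "82 patients per treatment group were deemed sufficient to achieve 80% power in detecting treatment differences", and the test is described as a "two-sided Chi-square test without continuity correction at a significance level of 0.025 (used to maintain the overall significance level at 5" percent. The dropout step follows: "Further, assuming a 15% dropout rate, we concluded that a total of 291 patients (97 per arm) would need to be recruited".

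The section Statistical analysis sets the analysis: "All efficacy and safety analyses will be conducted according to the intention-to-treat (ITT) principle", and "Missing values will be imputed by the last-observation-carried-forward method". The same section defines significance as a two-sided P value below 0.05. The article describes no completer or per-protocol analysis.

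The 40% for MZRW starts from the 43.3% seen in the team's placebo-controlled trial, which the Background describes: "In this study, 120 subjects were randomized into two arms (60 per arm").

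**The concern.** The power statement and the analysis do not match in two respects.

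- **Alpha.** The sample size section says the test is at two-sided 0.025, but 82 per arm is the answer for two-sided 0.05.
- **Analysis set.** Going from 82 to 97 protects a comparison of about 82 patients per arm with data. The planned comparison keeps all 97, dropouts included, with their missing values filled in. Its power depends on the response rates among all randomised patients, and the article does not say whether 40%, 20% and 10% are rates of that kind.

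What is at stake is the power for MZRW against senna, the comparison that this trial adds to the earlier placebo-controlled one. A reader who takes 80% at 0.025 from the text relies on a figure that fits neither 82 analysed at that level nor, except by coincidence, 97 analysed.

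**Working it through.** **Inputs.** From Sample size calculation: 40% v 20% (MZRW v senna), two-sided chi-square without continuity correction, alpha 0.025, 82 per arm, 15% dropout, 97 per arm. From Statistical analysis: intention to treat, last observation carried forward, two-sided 0.05. The text does not name the pair of arms behind the 82. I take it as MZRW v senna because that pair gives exactly 82 at two-sided 0.05, whereas at that level MZRW v placebo needs 32 and senna v placebo 199.

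**Formulas** (p̄ = mean of p1 and p2):

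- n per arm = [z(1−α/2)·√(2p̄(1−p̄)) + z(0.80)·√(p1(1−p1)+p2(1−p2))]² / (p1−p2)²
- power = Φ{ [√n·|p1−p2| − z(1−α/2)·√(2p̄(1−p̄))] / √(p1(1−p1)+p2(1−p2)) }

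For 40% v 20%: p̄ = 0.30, √(2×0.30×0.70) = 0.6481, √(0.24+0.16) = 0.6325. z(0.80) = 0.8416; z(1−α/2) is 1.9600 for 0.05 and 2.2414 for 0.025.

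**Step 1: the plan's own figures.**

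- Two-sided 0.05: (1.9600×0.6481 + 0.8416×0.6325)²/0.04 = 81.2, so 82. This is the stated number.
- Two-sided 0.025, as stated: (2.2414×0.6481 + 0.8416×0.6325)²/0.04 = 98.5, so 99.
- Dropout: 82/0.85 = 96.5, so 97; 3 × 97 = 291. Reproduced.

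**Step 2: power of 82 per arm.**

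- At 0.025: (√82×0.20 − 2.2414×0.6481)/0.6325 = 0.567, power 71.5% (72.3% by exact enumeration of the uncorrected chi-square).
- At 0.05: 0.855, power 80.4% (80.7% exact).

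**Step 3: power of the planned comparison, 97 per arm.** The article gives no response rate for dropouts, so rows 2 and 3 are assumptions.

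| Basis of the rates | MZRW v senna | Power at 0.025 | Power at 0.05 |
|---|---|---|---|
| 40% v 20% hold for all randomised | 40% v 20% | 79.3% (exact 80.1%) | 86.6% (exact 87.0%) |
| Completer rates; 15% dropouts respond at half the rate (factor 0.85 + 0.15×0.5 = 0.925) | 37% v 18.5% | 74.2% | 82.6% |
| Completer rates; 15% dropouts all non-responders (factor 0.85) | 34% v 17% | 68.6% | 78.0% |

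**Step 4: the dropout effect alone, alpha held fixed** (97 analysed minus 82 analysed at 40% v 20%).

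- At 0.025: 79.3 − 71.5 = +7.8 points; 74.2 − 71.5 = +2.7; 68.6 − 71.5 = −2.9.
- At 0.05: 86.6 − 80.4 = +6.2; 82.6 − 80.4 = +2.2; 78.0 − 80.4 = −2.4.

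Harsher assumptions go further down. If dropouts in both arms respond at the 10% placebo rate (35.5% v 18.5%), power is 66.8% at 0.025 and 76.4% at 0.05. If MZRW dropouts respond at the senna rate (37% v 20%), it is 65.1% and 75.0%. Nothing in the article supports these cases over the others.

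**Step 5: the source of the 40%.** The earlier trial's rates of 43.3%, 8.3%, 30.0% and 15.0% equal 26/60, 5/60, 18/60 and 9/60, with 60 randomised per arm. This suggests, without proving it, that 43.3% is a rate among all randomised patients, which points towards row 1.

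**The case against.** The dropout arithmetic is correct, and recruiting extra patients for dropout while planning an intention-to-treat analysis is common practice. Nowhere does the article say that dropouts are excluded. If 40% v 20% already hold for all randomised patients, as the sixtieths suggest, the extra 15 per arm are margin and raise power. All of this stands.

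A reader might infer something stronger: that dropout is wrongly counted twice, or that the trial really has only 69% power. The documents do not support that. Counting dropout twice, if it happened, would be conservative. The 69% needs every dropout to be a non-responder, which last observation carried forward does not imply: patients keep a daily diary, so someone who leaves mid-treatment has on-treatment data to carry forward. The 15% also has no stated timing. With an 8-week follow-up after treatment, some dropouts may complete the period on which the primary outcome rests. Most of the gap between 80% and 69% comes from alpha: at a fixed alpha, this scenario costs 2 to 3 points.

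It can also be said that an article may leave the basis of planning rates to a fuller document. That is fair, and the absence of that detail is not the point here. The point is a stated figure, 80% for 82 per arm at two-sided 0.025, which fails on its own inputs and is not tied to the analysis that the article sets out.

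**Conclusion.** The point holds in a limited form. At the stated two-sided 0.025, 82 per arm give about 72% power for 40% v 20%, not 80%; this follows from the stated inputs once the pair is taken as MZRW v senna. Separately, the planned comparison uses 97 per arm and the article gives no power for it. If 40% v 20% apply to all randomised patients, that power is about 79% (80% exact) at 0.025 or 87% at 0.05, so the enrolment target comes close to or exceeds the intended 80%. If dropouts dilute the rates, power could be about 74% or 69% at 0.025, and 83% or 78% at 0.05, but those figures rest on assumed dropout behaviour. The inflation to 97 is not an error. Its effect, from about −3 to +8 points in the three tabulated cases, cannot be signed from the article. The alpha mismatch is the larger and the provable part, and the two should be corrected together.

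**What to change.** In Sample size calculation, replace the sentence on 82 per arm with power for the 97 per arm analysed, at the alpha the trial will use. First reconcile the 0.025 there with the 0.05 in Statistical analysis. Possible text:

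- If 0.025 is kept: *With 97 patients per arm, all analysed by intention to treat, the uncorrected chi-square test of MZRW against senna at two-sided 0.025 has about 79% power (80% by exact enumeration) if response is 40% v 20% among all randomised patients. As a sensitivity assumption and not a prediction, if 15% drop out and respond at half the rate (37% v 18.5%) power is about 74%; if all are non-responders (34% v 17%), about 69%.*
- If 0.05 is kept: the same sentences with 87%, 83% and 78%, and with the remark about holding the overall level at 5% revised to match.

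The cost is a few sentences in one section plus agreement on alpha. Enrolment stays at 291. The stated power will look less favourable if 0.025 is kept. According to Trial status, 20 subjects had been enrolled and none had completed treatment at submission, so the correction could be made before any outcome was known.

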### Statistical analysis

All efficacy and safety analyses will be conducted according to the intention-to-treat (ITT) principle. Missing values will be imputed by the last-observation-carried-forward method. The statistical analysis will be performed using the Statistical Packages of Social Sciences (SPSS) for Windows version 16.0. The statistical significance is defined as two-sided *P* value of <0.05. Baseline characteristics will be reported as mean (SD). Baseline differences among the groups will be assessed with the use of Student’s t-test for normally distributed continuous variables and the non-parametric Mann-Whitney U test for non-normally distributed variables. For categorical variables, chi-squared test or Fisher’s exact test will be used. Comparisons between groups will be conducted by using an analysis of covariance (ANCOVA) with baseline as covariate. All items and subscales will be compared between groups for each 6-week treatment using ANCOVA, with treatment group as a factor in the model and baseline as the covariate. The changes from baseline to endpoint of treatment in scores will be tested with repeated measure analysis of variance (ANOVA). Within group differences will be assessed with paired t-test for normally distributed data and Wilcoxon signed-rank test for non-normally distributed data.

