**Schedule of enrolment, ****intervention and assessments.**

### Participants

*Setting*: The study was performed at Lee Kee Memorial Dispensary (general outpatient clinic), Li Ka Shing Specialist Clinic of Prince of Wales Hospital and Clinics of the School of Chinese Medicine, and Hong Kong Baptist University. The participants were enrolled from the public through advertisements in local newspaper and out-patient clinics.

*Diagnostic criteria for FC* (*Rome III*) [3]: 1) At least two of the following occurrences more than 25% of the time were required for a diagnosis of functional constipation: straining, lumpy or hard stools, sensation of incomplete evacuation, sensation of anorectal obstruction/blockage, manual maneuvers to facilitate, or fewer than three defecations per week; as well as 2) the rare presence of loose stools without the use of laxatives; and also 3) insufficient criteria for a diagnosis of irritable bowel syndrome.

*Diagnostic criteria for excessive constipation in TCM theory*[6]: Any three of the chief symptom manifestations of Heat and/or Qi stagnation were required for a diagnosis of functional constipation: 1) dry, hard stools; 2) difficult bowel movements; 3) abdominal distension, with or without tenderness; 4) belching; 5) dry mouth or halitosis; 6) red tongue with dry and/or yellow coating; and 7) Wiry pulse.

*Inclusion Criteria*: Patients were included if they had all of the following: 1) met the diagnostic criteria for FC (Rome III); 2) met the diagnostic criteria for excessive constipation in TCM theory; 3) were age 18 to 65 years (inclusive); 4) had a complete spontaneous bowel movement (CSBM) ≦2 times/week (CSBM is defined by feeling of complete passage of stool after defecation, rather than partial or incomplete evacuation, without the use of any laxative or enema within 24 hours) [19]; 5) exhibited severity of constipation ≧3 points (on a 7-point scale) [20]; 6) had a total symptom score ≧8 points (on a 7-point scale for constipation-related symptoms); 7) had a normal colonic examination (barium enema or colonoscopy) within five years; and 8) had a normal liver and renal function in blood test within 3 months.

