Secondary outcomes will include the response rate for CSBM during the follow-up period, including stool frequency, changes from baseline in scores of individual symptom assessment (severity of constipation, sensation of straining, incomplete evacuation, bloating, cramping/abdominal pain, nausea and passing of gas), and global symptom assessment (improved, same or worse). Safety profiles of MZRW will be assessed by determining important adverse events reported in participants’ diaries, in follow-up interviews and in clinical laboratory evaluations (for example, liver and renal function testing). During the last visit, the success of blinding would be evaluated for both investigators and patients, as to whether CHM, WM or placebo had been taken. In particular, patients are asked to rate the appearance, color, texture, taste and efficacy of the medication to try to determine whether these factors were important in their conclusion.

In addition, an objective estimate of changes in colonic transit time is made based on a commercially available radio-opaque Sitzmarks capsule (Konsyl Pharmaceuticals, INC.,Easton, MD 21601,U.S.A).

Each gelatin capsule contains 24 barium sulfate embedded polyvinyl chloride markers measuring 1 mm × 4.5 mm. Plain radiographs of the abdomen are obtained after patients swallow a capsule, for five days (120 hours) before and 8 weeks after the treatment period. Normal colonic transit is defined as expulsion of at least 80% (19 or more) markers [27,28]. For patients with six or more makers scattered throughout the colon, hypomotility or colonic inertia is suggested. If six or more markers are gathered in the rectosigmoid region with a near normal transit of markers through the rest of the colon, functional obstructive or dys-synergic defecation is suspected [4,29].

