### Recruitment procedures

Three strategies are used to recruit participants with FC. The first relies on the participant bank of over 600 patients, built up from prior research team work in functional constipation related studies since 2007. The second relies on referrals from the two study sites (Lee Kee Memorial Dispensary and Li Ka Shing Specialist Clinic of Prince of Wales Hospital) from our co-investigators (Co-Is). The third strategy consists of posted advertisement in local newspapers and a press conference to introduce our research.

All patients diagnosed with functional constipation by the physicians (Co-Is) are referred to the principal investigator (PI) and/or to the research assistants (RA) to determine whether they meet diagnostic criteria of excessive constipation according to TCM theory. There is inconsistency among different TCM practitioners regarding pattern differentiation for FC. If any inconsistency occurs for an individual patient concerning pattern identification, the other senior CMP with more than 20 years clinical practice will be invited to make the diagnosis of TCM pattern independently to ensure the consistence of the diagnosis. The aims, procedures and nature of the study, and possible side effects are explained by the PI and/or the RAs before a written consent form is obtained from each subject who agrees to participate. Moreover, patients are informed that they are free to withdraw at any time during the study. All patients undergo a 2-week, drug-free observation period. Meanwhile, they have to complete a stool and symptom diary to confirm their diagnosis. Blood tests of liver and renal function (blood urea, creatinine, alanine transaminase and aspartate transaminase, alkaline phosphatase and bilirubin), and plain abdominal X-ray for colonic transit study are arranged. Patients are considered eligible for the study if their diaries reflect conformance with the Rome III criteria for a diagnosis of functional constipation, and if they also have normal liver and renal function. Recruited patients will obtain their intervention assignment from the PI and/or RAs.

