### Data collection and handling of withdraw and dropout

This is an 18 week clinical trial, in which subjects need to take research medication for 8 weeks, attend 5 assessment visits, obtain 2 sets of blood tests and plain abdominal X-rays, fill in a few sets of questionnaires, complete a patient diary for the entire study period, and stop taking other herbal medication and laxatives. Original data of study forms will be entered and kept on file at the participating site. All the files are to be stored in numerical order and stored in a secure and accessible place. Participant files will be maintained in storage for a period of 5 years.

In order to maximize subjects’ compliance, we first run a thorough consent process for all participants by explaining the details of the study schedule, potential side effects of treatment, and the responsibilities that need to be undertaken by subjects. Second, support and reassurance is provided during the whole study. Third, we will carefully scrutinize subjects (during the 2-week run-in period) to exclude ineligible and potentially low compliance individuals before randomization. Fourth, a direct telephone hotline and email account were established in order to optimize active communication with patients and to respond to enquiries. Furthermore, additional visits can be arranged for patients to see WM doctors or TCM practitioners if patients develop adverse events before the next scheduled visit. If any patient expressed thoughts of withdrawing or dropping out, we would try to help that individual determine the reason, and attempt to resolve any issues, in order to keep the patient in the study.

In order to monitor the reported compliance of the patients, the patients will be required to return the remaining medications at treatment visits except the first visit and last visit. Our research assistant will take a record of each patient. 80% of the consumption will be considered good compliance. If the patients have no bowel movement for at least three consecutive days during the study rescue therapy as dulcolax suppository are provided to the patients.

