The trial would be terminated in a specific subject if he/she has: 1) presence of severe adverse effect; 2) hypersensitivity towards research medication; 3) participation in another CHM research project; or 4) presence of life-threatening disease. The whole research plan would be terminated for the following circumstances: 1) presence of serious adverse effect related to the research medication with supportive evidence; or 2) completion of all follow-up assessments.

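### Applying ITT and last-observation-carried-forward to safety data records patients without a second blood test as normal, diluting laboratory abnormality rates

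*Protocol article*

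**What the plan says.** Two consecutive sentences in the Statistical analysis section of the protocol article set the rules. The first is "All efficacy and safety analyses will be conducted according to the intention-to-treat (ITT) principle". The second is "Missing values will be imputed by the last-observation-carried-forward method", which is not confined to efficacy. The article names no separate safety population and no observed-case rule for laboratory values.

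Other sections determine what these rules do to laboratory data:

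- **Outcomes:** safety covers adverse events from diaries, and also those found "in follow-up interviews and in clinical laboratory evaluations (for example, liver and renal function testing" and the like.
- **Data collection and handling of withdraw and dropout:** each subject will "obtain 2 sets of blood tests and plain abdominal X-rays", so there are two laboratory time points.
- **Participants, inclusion item 8:** patients must have "had a normal liver and renal function in blood test within 3 months".
- **Recruitment procedures:** blood tests are arranged around the run-in, and patients are eligible only "if they also have normal liver and renal function".
- **Sample size calculation:** the total is obtained by "assuming a 15% dropout rate".

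**The concern.** Carrying the last observation forward needs an earlier observation that says something about the missing one. Here the only earlier scheduled laboratory value is pre-treatment and normal by the entry rule. For a patient without the second set, the rule can only produce a normal classification, or zero change on a continuous scale. It can hide an abnormality but cannot create one.

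The ITT rule then keeps that patient in the denominator as though tested. It also keeps randomised patients who took no drug in the denominator for adverse events.

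The safety of the herbal granules is an aim in the Background and an expected conclusion in the Conclusions. At stake is a laboratory safety statement that rests partly on results nobody measured. If dropout is similar across arms, differences between arms shrink as well.

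**Working it through.** **Inputs from the protocol article.** 82 evaluable patients per arm, 15% dropout, 97 per arm and 291 in total (Sample size calculation); two blood sets (Data collection and handling of withdraw and dropout); normal liver and renal function at entry (Participants; Recruitment procedures).

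**Assumed.** The article gives no laboratory abnormality rate, so r, the rate among patients with a second set, is assumed. It gives no count of patients who would miss the second set, so the 15% dropout allowance serves as an upper planning figure.

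**Step 1: reproduce the plan's dropout step.** 82 / 0.85 = 96.5, rounded up to 97; 3 × 97 = 291. Both agree with the article. Then 97 × 0.15 = 14.6, so about 15 per arm would lack a second set and 82 would have one.

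**Step 2: dilution of the abnormality rate.** Each of the 15 is scored normal.

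- Observed-case rate = 82r / 82 = r
- Rate under ITT with carrying forward = 82r / 97 = 0.845r, about 0.85r

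| Assumed r | Observed cases | ITT with carrying forward |
|---|---|---|
| 2% | 2.0% | 1.7% |
| 5% | 5.0% | 4.1 / 97 = 4.2% |
| 10% | 10.0% | 8.5% |

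For a missing fraction d the factor is 1 − d: 0.95 if 5% lack the second set and 0.75 if 25% do. A mean change from baseline shrinks by the same factor, because the imputed changes are zero.

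**Step 3: no abnormalities seen.** The one-sided 95% upper bound is 1 − 0.05^(1/n).

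- n = 97: 3.04%
- n = 82: 3.59%

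**Step 4: what the observed-case rule does not repair.** Suppose 5% of completers and 20% of dropouts would be abnormal. The rate over all 97 is (4.1 + 3.0) / 97 = 7.3%. Carrying forward reports 4.2% and observed cases report 5.0%. The change recovers 0.8 of the 3.1-point gap. With 40% in dropouts the all-patient rate is (4.1 + 6.0) / 97 = 10.4%, and the change recovers 0.8 of 6.2 points. The remainder is informative dropout.

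**Step 5: adverse events.** Events are counted as reported, so Step 2 does not apply. Only never-treated patients dilute the rate. Their number is not given; if it were 2 to 10 of 97, the factor would be 95/97 = 0.98 to 87/97 = 0.90.

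**The case against.** **Detail left to the analysis plan.** Missing-data rules for laboratory values usually belong in the SAP, and a general imputation sentence may have been written with efficacy in mind. That would answer a complaint that something is missing. Here, though, the first sentence names safety explicitly and the second has no limit, so the text as written gives the result above.

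**Size.** A reader might infer that the plan hides a true rate of 7.3% or 10.4% behind a reported 4.2%. The documents do not support that. The dropout rates behind those figures (20% and 40%) are four and eight times the assumed completer rate, and nothing in the article backs them. Early leavers have less exposure, so the multiple could be below 1: at half the completer rate the reported-to-true ratio is 0.85 / (0.85 + 0.075) = 0.92, and at zero there is no bias. Most of those gaps would also remain under observed-case analysis.

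**Toxicity in general.** A reader might also infer that both rules push all safety rates down. Adverse events reported before withdrawal still count. A severe adverse effect is itself a ground for ending participation ("The trial would be terminated in a specific subject if he/she has: 1) presence of severe adverse effect"), so it would be known. Analysing a misdispensed patient in the assigned arm can move a rate either way.

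**Facts not in the text.** The second blood set is not dated and the schedule figure is not shown, so calling it on-treatment would be an inference. The 15% is a sample-size allowance; some dropouts may still be tested, including at the extra visits offered for adverse events. The article also plans no explicit laboratory proportion or safety interval, so the figures in Steps 2 and 3 are illustrations.

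These limits reduce the size and scope of the point. They do not change what happens to a patient with one normal value and no second one.

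**Conclusion.** The point holds for laboratory safety data. As written, the plan assigns a normal or unchanged result to anyone without a second blood set. If all planned dropouts lacked it, abnormality rates would fall to about 0.85 of the observed-case rate, which is 0.8 percentage points at an assumed 5%, and a zero-event bound would read 3.0% where the tested patients support 3.6%. These figures rest on the 15% allowance as an upper planning figure and on an assumed abnormality rate. The mechanism itself needs only two sets with the first normal.

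For adverse events only the denominator point remains, and it is probably small. A broader conclusion that the plan understates toxicity by several percentage points is not supported: it would need informative dropout of a size the documents do not give.

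**What to change.** Limit the ITT and carrying-forward sentences to efficacy. Add that safety will be analysed in patients who took at least one dose, grouped by treatment received. Report laboratory values as observed, without carrying forward, and show the number tested per arm.

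This is an edit of two sentences, with no extra patients, visits or tests. The cost is slightly smaller safety denominators and wider intervals. Because the change does not correct for dropout related to harm, the number tested should be shown beside each laboratory result so that readers can see how many patients are unaccounted for.
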